**Figure 2 F2:**
[figure not shown]
Classification using spirometry and FeNO measurement. BD, bronchodilator; COPD, chronic obstructive pulmonary disease; FeNO, fractional exhaled nitric oxide; FEV₁, forced expiratory volume in the first second; FVC, forced vital capacity; PRISm, Preserved Ratio Impaired Spirometry.

Abnormal spirometry or diagnosis of CRD includes COPD, asthma, asthma-COPD overlap, PRISm, restriction patterns, asthma-PRISm overlap and asthma-restriction overlap.Normal spirometry: Participants without lung function abnormalities.

Those with abnormal spirometry results or a diagnosis of CRD in MARES-1 will receive their results, interpreted by a local pulmonologist using local Pereira reference equations^43^ along with educational materials co-developed with support from our PPI group, providing guidance on diagnosis, risk factors, symptoms and recommendations to seek appropriate healthcare services. For participants with asthma overlapping COPD, restrictive patterns or PRISm, asthma will be considered the primary condition for the purposes of health guidance and analysis.

CAAT and ACQ-7 questionnaires: After FeNO measurement and spirometry (MARES-1 and MARES-3), all individuals with abnormal spirometry or diagnosis of CRD will complete the CAAT questionnaire and will be asked about their history of previous exacerbations. Individuals diagnosed with asthma (isolated or overlapping with other conditions) will additionally complete the ACQ-7 questionnaire (MARES-1 and MARES-3). Both questionnaires have been validated for use in the Brazilian population.^34 36^ The CAAT questionnaire is used to assess the impact of CRD symptoms on daily life. It consists of eight items addressing cough, phlegm, chest tightness, dyspnoea when walking up a hill or one flight of stairs, limitations in daily activities, confidence in leaving the house, sleep quality and energy levels. Each item is scored from 0 to 5, with individuals selecting one answer per item. The total score (maximum of 40 points) indicates the clinical impact of the disease: 6–10 points: mild; 11–20 points: moderate; 21–30 points: severe; and 31–40 points: very severe.^34^ The ACQ-7 questionnaire assesses asthma control over the previous week. It includes six questions on asthma symptoms and short-acting bronchodilator use (each scored from 0 to 6) plus a measure of prebronchodilator forced expiratory volume in one second (FEV_1_ % predicted), also scored from 0 to 6. The final score is the average of all seven items, with values <0.75 indicating controlled asthma and values ≥1.5 indicating uncontrolled asthma.^34^

Fidelity monitoring and interview with health professionals: During the administration of the COLA-6 questionnaire, the researcher will observe the beginning and at the end of all applications by the healthcare professional to evaluate fidelity in the application process (MARES-2). The researcher will observe the application technique of questions and peak flow, total application time, accuracy of scoring and whether the educational leaflet was correctly provided. If any inconsistency or error is identified in the first application, the researcher will intervene and provide guidance for correction in subsequent assessments.^44^ After administering the COLA-6 to 50 patients, each healthcare professional will participate in a face-to-face, semistructured interview conducted by the UFSCar research team. These interviews aim to explore barriers and facilitators related to implementing the tool in a real-world PHC setting. Interviews will be audio-recorded, transcribed verbatim and anonymised prior to analysis. The questions (provided in the online supplemental material) will address feasibility aspects such as the time required to complete the questionnaire, difficulties encountered, clarity of the questions, uncertainties during application integration of the tool into the work routine and patient receptiveness. Additionally, data will be collected to characterise each healthcare professional, including their profession, age, sex, length of professional training and years of work at the BHU/FHU.

Interview with patients: In MARES-3, semistructured interviews will be conducted with a sample of 30 patients diagnosed with abnormal spirometry or diagnosis of CRD and high risk for CRDs previously identified in MARES-1 and MARES-2, respectively: 10 with COPD, 10 with asthma and 10 with PRISm or restriction. These face-to-face interviews will be open-ended questions, audio-recorded, transcribed and anonymised before analysis. Participants will be selected to ensure diversity in gender, age, socioeconomic status and employment background. The interview (questions included in the online supplemental material) will explore how participants accessed healthcare services for diagnostic confirmation and treatment, and how this process affected their health status. Topics will include barriers and facilitators encountered, how doubts were clarified, the type of education they received regarding the disease, diagnosis and treatment, and whether any changes occurred in their lifestyle or routine following diagnosis or treatment. Additionally, a quantitative questionnaire will be administered to all participants to collect information on healthcare access, type of treatment received, medication access and treatment adherence.

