**Methods and analysis:**

The Multimorbidity Approach for REspiratory Solutions (MARES) study consists of three work packages to be conducted in PHC services in São Carlos/SP and São Paulo/SP, Brazil.

MARES-1: A cross-sectional observational study enrolling 859 individuals with at least one NCD receiving care in PHC. The COLA-6 questionnaire will be administered by the research team and compared with quality-assured spirometry. The Chronic Airways Assessment Test (CAAT), Asthma Control Questionnaire (ACQ-7) and fractional exhaled nitric oxide (FeNO) will also be assessed. The diagnostic performance of COLA-6 for identifying CRDs—including COPD, asthma, preserved ratio impaired spirometry, restriction and overlaps—will be assessed using area under receiver operating characteristic curves and 95% CIs.

MARES-2: A cross-sectional observational study enrolling 20 healthcare professionals (physicians, physiotherapists, community health agents and nurses) from five PHC services. These professionals will apply the COLA-6 during routine NCD care to a total sample of 1000 patients. Qualitative interviews will be conducted to explore barriers and facilitators to the implementation of COLA-6, using deductive thematic analysis.

MARES-3: A longitudinal, prospective observational study in which patients from MARES-1 and MARES-2 will be reassessed at 6-month follow-up. A total sample of 473 participants with abnormal spirometry, a diagnosis of CRD or high risk for CRDs is expected. Participants will undergo spirometry, and a subset will be interviewed to explore their healthcare experiences through qualitative thematic analysis. Access to diagnostic and treatment services in Brazil will be assessed. Changes in spirometry values, FeNO, CAAT and ACQ-7 scores from baseline to 6 months in patients from MARES-1 will be analysed.

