### Statistical methods

#### Sample size

MARES-1: The sample size calculation was based on the performance of the COLA-6 questionnaire for diagnosing COPD in the GECo study (sensitivity: 45.7%; specificity: 86.5%) and assuming a COPD prevalence of 17% in Brazil.^45^ With these assumed values, a minimum sample size of N=859 individuals will allow us to estimate the area under the ROC curve (AUC) to within 4.5% (based on a 95% CI). According to prevalence studies for CRDs in Brazil, we calculate that we will identify approximately 146 individuals with COPD, 77 with asthma and 86 with Preserved Ratio Impaired Spirometry (PRISm) or restriction in this study, giving an estimated sample of 309 with abnormal spirometry and 550 with normal spirometry. We will case-find in more people if the expected prevalence is lower to reach these targets.

MARES-2: The number of BHU/FHU that will be involved in this study, as well as the number of health professionals (N=20) responsible for applying the COLA-6 questionnaire, was a pragmatic decision. Based on the GECo study,^19^ of the total individuals evaluated (N=1000), we anticipate that 16.4% (N=164) will be identified as at high risk for CRDs (COLA-6≥4) and 836 will be identified as at low risk for CRDs. We will case-find in more people if the expected prevalence is lower to reach these targets.

MARES-3: The sample size expected (N=473) is dependent on samples obtained from MARES-1 and MARES-2. Considering the prevalence found in the GECo study^19^ and prevalence available for the Brazilian population, we estimate that we will have up to 218 individuals with COPD, 100 with asthma and 100 with PRISm.

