### Data analysis

MARES-1: We will summarise the demographic and clinical characteristics of participants overall. Based on spirometry results, we will report the prevalence of COPD, asthma, PRISm and restriction, alone and in combination, with 95% CIs. For the primary analysis, we will calculate the AUC of the ROC curves for COLA-6 compared with the gold standard spirometry diagnosis separately for combined CRDs, asthma, COPD, PRISm and restriction. Using the previously published threshold for COLA-6 scores of ≥4,^19^ we will also calculate sensitivity, specificity, and negative and positive predictive values. In addition, based on the ROC curve, we will identify the COLA-6 score threshold that achieves sensitivity of at least 90%. Similar AUC analyses will be conducted for SBQ and results compared with those for COLA-6.

MARES-2: Descriptive statistics will be used to characterise the patient and healthcare professional demographics. Quantitative analysis will assess fidelity data, with categorical variables reported as frequencies (percentages). The qualitative analysis of the interviews will follow Braun and Clarke,^46^ which consists of six phases: (1) familiarisation with the data set; (2) coding; (3) generation of initial themes; (4) development and review of themes; (5) refinement, definition and naming of themes and (6) writing. The initial analysis of the transcripts obtained from the interviews will be carried out using the Web Qualitative Data Analysis software (University of Aveiro, Aveiro, Portugal) and completed manually using a Microsoft Excel spreadsheet. To ensure reliability, the criteria of credibility, transferability, dependability and confirmability will be used.^47^

MARES-3: Descriptive statistics will be used to describe the individual samples from MARES-1 and MARES-2. For patients from MARES-2, the proportions diagnosed with CRDs at spirometry will be calculated. For individuals in MARES-1, who have longitudinal data, the mean change in spirometric values from baseline to 6 months will be summarised and the proportion with improved values will be reported. Additionally, baseline and 6-month CAAT and ACQ-7 questionnaire scores, and FeNO will be summarised and mean changes reported. Estimates will be provided with 95% CIs. The qualitative analysis of the interviews will follow Braun and Clarke,^46^ as described above for MARES-2.

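### The asthma-first rule extends to analysis, which conflicts with separate primary ROC curves for COPD, PRISm and restriction: overlap participants end up either in the comparator group or lost from the cases

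*Protocol article*

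**What the plan says.** Four places in the protocol article bear on this.

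- **Assessments, text under Figure 2.** The abnormal group is made up of "COPD, asthma, asthma-COPD overlap, PRISm, restriction patterns, asthma-PRISm overlap and asthma-restriction overlap", so overlaps are recognised as classes. For the overlaps with asthma, the same section then says "asthma will be considered the primary condition for the purposes of health guidance and analysis".
- **Data analysis, MARES-1.** Prevalence will cover the "prevalence of COPD, asthma, PRISm and restriction, alone and in combination". The primary analysis gives AUCs for COLA-6 against the spirometry diagnosis "separately for combined CRDs, asthma, COPD, PRISm and restriction". The text does not say whether an overlap participant is a case, a comparator or excluded in each curve. Nor does it say whether the comparator is normal spirometry or everyone without the condition.
- **Sample size, MARES-1.** N=859 is justified by COLA-6 performance for COPD, "assuming a COPD prevalence of 17% in Brazil". The expected yield is that "we will identify approximately 146 individuals with COPD, 77 with asthma and 86 with Preserved Ratio Impaired Spirometry (PRISm) or restriction", which gives 309 abnormal and 550 normal.
- **Abstract, Methods and analysis.** The targets for diagnostic performance are listed as "including COPD, asthma, preserved ratio impaired spirometry, restriction and overlaps".

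**The concern.** An asthma-first label may serve a leaflet or a one-label table. The protocol extends it to the analysis, and the primary analysis has a separate curve for each condition. A participant who meets the COPD criteria and also has asthma is relabelled asthma. In the COPD curve that person must then be a non-case, which misclassifies the reference standard, or be left out, which removes a COPD case and narrows the case mix. Only setting the rule aside avoids both. PRISm and restriction are affected in the same way.

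At stake is the COPD curve, the one for which N=859 was sized, together with the smaller PRISm and restriction curves. If the case definition is settled only after the data are seen, the choice can also be influenced by which version performs better.

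**Working it through.** **1. The plan's own counts.** 859 × 0.17 = 146.0; 146 + 77 + 86 = 309; 859 − 309 = 550. All reproduce. The groups add up as mutually exclusive, with no overlap class, yet 146 is the full 17% of the sample with nothing taken out. Under an asthma-first label fewer than 146 would be labelled COPD, unless the 17% already excludes overlaps. The document does not say whether it does.

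**2. A starting AUC.** The protocol gives sensitivity 45.7% and specificity 86.5% but no AUC. An equal-variance binormal curve through that point has d = Φ⁻¹(0.457) + Φ⁻¹(0.865) = −0.108 + 1.103 = 0.995, so AUC = Φ(0.995/√2) = 0.759, rounded to 0.76. This value is an assumption. With 146 cases and 713 others, the Hanley-McNeil 95% half-width is 4.8 points. The stated 4.5% depends on the method: 4.2 from the variance of (sensitivity + specificity)/2 at a single cut-off, and 4.5 from Hanley-McNeil at AUC 0.80. The point does not depend on it.

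**3. The rule with everyone else as comparator.** Let f be the share of the 146 COPD cases who also have asthma. It is not given; 10%, 20% and 30% are assumed. Then k = 146f = 14.6, 29.2 or 43.8 people change sides. Non-cases score N(0,1), isolated COPD N(m,1) and overlaps N(m+δ,1). The AUC that counts any COPD as a case is held at 0.76:

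(1−f)Φ(m/√2) + fΦ((m+δ)/√2) = 0.76

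The AUC under the rule is

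[713·Φ(m/√2) + k·Φ(−δ/√2)] / (713 + k)

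Worked example with f = 30% and δ = +0.5: m = 0.862, Φ(m/√2) = 0.729, Φ(−0.5/√2) = 0.362. AUC = (713 × 0.729 + 43.8 × 0.362)/756.8 = 0.708, a shift of −0.052.

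| Overlap share f | 10% | 20% | 30% |
|---|---|---|---|
| Cases labelled COPD | 131 | 117 | 102 |
| AUC, overlaps score like other COPD (δ = 0) | 0.755 | 0.750 | 0.745 |
| AUC, overlaps 0.5 SD higher | 0.742 | 0.725 | 0.708 |
| AUC, overlaps 0.5 SD lower | 0.769 | 0.778 | 0.785 |
| Half-width in points, 0.5 SD higher | 5.1 | 5.5 | 5.9 |

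**4. The rule with overlaps excluded.** The comparator stays clean and the AUC is Φ(m/√2), that of isolated COPD alone. It remains 0.76 if overlaps score like other COPD. At f = 30% it is 0.729 if overlaps score 0.5 SD higher and 0.794 if 0.5 SD lower. The case count falls as in the table.

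**5. What does not move.** An overlap participant has a CRD under any label, so the combined-CRD curve is the same in every scenario.

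**The case against.** The strongest reply is that nothing in the protocol says overlap participants become non-cases. Calling asthma primary need not delete the COPD classification, overlaps are listed as classes of their own, the comparator is unstated, and Figure 2 is not shown. A single label also has legitimate uses, such as filling the interview groups in MARES-3. Exact case and comparator sets are often left to a SAP.

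Much of this stands, and it rules out several stronger readings that a reader might infer:

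- **That overlaps certainly contaminate the comparator group.** This needs both label removal and an all-others comparator, and the document fixes only a primary label.
- **That the prevalences will be biased.** The commitment to report conditions alone and in combination keeps overlaps visible, and any-COPD prevalence can be recovered.
- **That the AUC will be lowered.** The sign depends on how overlap participants score, which is not given.
- **That comparability with the GECo study is broken.** This would require knowing how that study handled asthma overlap, which the documents do not say.

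The reply does not remove the conflict. The complaint is not that a detail is missing: the published text states a rule, extends it to analysis, and plans primary curves that the rule does not fit. Counting overlaps under every condition they meet would be sound, but it means not following the rule. A SAP that followed it literally would carry the problem forward.

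**Conclusion.** The point holds as a conflict between the Assessments and Data analysis sections that should be reconciled before analysis. If followed, the asthma-first rule causes either misclassification or loss of cases in the COPD, PRISm and restriction ROC analyses. It also sits badly with reporting conditions in combination and with naming overlaps as diagnostic targets.

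The size cannot be fixed from the document. The shift in the COPD AUC is zero if there is no overlap. With an all-others comparator and 10–30% overlap, it is −0.005 to −0.015 if overlaps score like other COPD, −0.018 to −0.052 if they score 0.5 SD higher, and +0.009 to +0.025 if 0.5 SD lower. Only the extreme of these scenarios (30% overlap scoring 0.5 SD higher) exceeds the stated 4.5% precision. These figures rest on an assumed AUC of 0.76, a binormal score model and assumed overlap rates. The combined-CRD AUC is not affected.

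**What to change.** Limit the asthma-first rule to health guidance and to any description that needs one label per person, and remove its application to the ROC analyses. Then state in Data analysis, MARES-1, for each condition-specific ROC analysis:

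- **Cases:** every participant who meets that condition's criteria, whether isolated or overlapping.
- **Comparator:** participants without that condition.
- **Sensitivity analysis:** isolated disease only.

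In the sample size section, say whether the 17% and the 146 expected COPD cases include asthma-COPD overlap.

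The cost is a few sentences in the protocol or SAP. No new data, visits or participants are needed, because the classification already records the overlaps.

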### Data management

All procedures will comply with the Brazil General Personal Data Protection Law, Law No. 13,709/2018 and UK General Data Protection Regulation. This includes adherence to standard operating procedures designed to preserve the confidentiality, integrity and availability of information. Data will initially be collected using paper case report forms (CRFs) before being entered into a REDCap database. During this process, all data will be pseudonymised to ensure security and privacy for both patients and participating healthcare professionals. The paper forms, which contain patient identifiers, will be securely stored in a locked file cabinet, separate from other data collections, in a locked room at the Cardiopulmonary Physiotherapy Laboratory of the Department of Physiotherapy at UFSCar, under the responsibility of the Brazil-based principal investigator.

Data management and curation will be overseen by the lead researcher at UFSCar ([name]), the project manager ([name]) and the postdoctoral fellow at UFSCar ([name]). After 10 years, all paper forms will be destroyed by shredding. Deidentified datasets required for reproducing the prespecified analyses will be made available via Research Electronic Data Capture (REDCap) to both the UFSCar and UCL research teams. Electronic CRFs will be stored on REDCap, a Good Clinical Practice (GCP) compliant database used by UCL. Additionally, the entire UFSCar research team will receive comprehensive training on data collection and storage procedures, as well as training in good research practices.

### Statistical methods

#### Sample size

MARES-1: The sample size calculation was based on the performance of the COLA-6 questionnaire for diagnosing COPD in the GECo study (sensitivity: 45.7%; specificity: 86.5%) and assuming a COPD prevalence of 17% in Brazil.^45^ With these assumed values, a minimum sample size of N=859 individuals will allow us to estimate the area under the ROC curve (AUC) to within 4.5% (based on a 95% CI). According to prevalence studies for CRDs in Brazil, we calculate that we will identify approximately 146 individuals with COPD, 77 with asthma and 86 with Preserved Ratio Impaired Spirometry (PRISm) or restriction in this study, giving an estimated sample of 309 with abnormal spirometry and 550 with normal spirometry. We will case-find in more people if the expected prevalence is lower to reach these targets.

MARES-2: The number of BHU/FHU that will be involved in this study, as well as the number of health professionals (N=20) responsible for applying the COLA-6 questionnaire, was a pragmatic decision. Based on the GECo study,^19^ of the total individuals evaluated (N=1000), we anticipate that 16.4% (N=164) will be identified as at high risk for CRDs (COLA-6≥4) and 836 will be identified as at low risk for CRDs. We will case-find in more people if the expected prevalence is lower to reach these targets.

MARES-3: The sample size expected (N=473) is dependent on samples obtained from MARES-1 and MARES-2. Considering the prevalence found in the GECo study^19^ and prevalence available for the Brazilian population, we estimate that we will have up to 218 individuals with COPD, 100 with asthma and 100 with PRISm.

### Data analysis

MARES-1: We will summarise the demographic and clinical characteristics of participants overall. Based on spirometry results, we will report the prevalence of COPD, asthma, PRISm and restriction, alone and in combination, with 95% CIs. For the primary analysis, we will calculate the AUC of the ROC curves for COLA-6 compared with the gold standard spirometry diagnosis separately for combined CRDs, asthma, COPD, PRISm and restriction. Using the previously published threshold for COLA-6 scores of ≥4,^19^ we will also calculate sensitivity, specificity, and negative and positive predictive values. In addition, based on the ROC curve, we will identify the COLA-6 score threshold that achieves sensitivity of at least 90%. Similar AUC analyses will be conducted for SBQ and results compared with those for COLA-6.

MARES-2: Descriptive statistics will be used to characterise the patient and healthcare professional demographics. Quantitative analysis will assess fidelity data, with categorical variables reported as frequencies (percentages). The qualitative analysis of the interviews will follow Braun and Clarke,^46^ which consists of six phases: (1) familiarisation with the data set; (2) coding; (3) generation of initial themes; (4) development and review of themes; (5) refinement, definition and naming of themes and (6) writing. The initial analysis of the transcripts obtained from the interviews will be carried out using the Web Qualitative Data Analysis software (University of Aveiro, Aveiro, Portugal) and completed manually using a Microsoft Excel spreadsheet. To ensure reliability, the criteria of credibility, transferability, dependability and confirmability will be used.^47^

MARES-3: Descriptive statistics will be used to describe the individual samples from MARES-1 and MARES-2. For patients from MARES-2, the proportions diagnosed with CRDs at spirometry will be calculated. For individuals in MARES-1, who have longitudinal data, the mean change in spirometric values from baseline to 6 months will be summarised and the proportion with improved values will be reported. Additionally, baseline and 6-month CAAT and ACQ-7 questionnaire scores, and FeNO will be summarised and mean changes reported. Estimates will be provided with 95% CIs. The qualitative analysis of the interviews will follow Braun and Clarke,^46^ as described above for MARES-2.

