##### Phase 1: Implementation of COLA-6

Application of COLA-6 questionnaire: After receiving prior training from the UFSCar research team, healthcare professionals at the BHUs and FHUs will identify potentially eligible individuals with NCDs who attend PHC services and will administer the COLA-6 questionnaire as part of their routine care. Participants identified as high risk for CRDs based on COLA-6 results will be provided with an informational leaflet containing basic guidance about pulmonary health and how to access diagnostic and treatment services for respiratory conditions.

Fidelity monitoring: The research team at the UFSCar will observe the administration of the COLA-6 at the beginning and end of all applications by each healthcare professional to ensure adherence to the protocol.

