##### Phase 2: Participant enrolment and assessment

Following the administration of the COLA-6 as part of routine care, healthcare professionals will inform individuals who meet the inclusion criteria about the research and invite them to participate. Individuals expressing interest will be referred to the research team, who will subsequently contact them to provide detailed study information and obtain written informed consent. On consent, the research team will conduct the initial assessment (details below).

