### MARES-3

Participants with abnormal spirometry or diagnosis of CRD from MARES-1 and those identified as high risk for CRDs in MARES-2 will be contacted for a follow-up visit 6 months after their initial participation. Follow-up will take place at the respective BHUs/FHUs and will be conducted by the UFSCar research team in a single day. Multiple contact options will be collected at baseline, and up to three telephone attempts will be made at follow-up; participants lost to follow-up will be documented and analysed. Procedures include:

FeNO measurement.Spirometry (prebronchodilator and postbronchodilator).Application of disease-specific questionnaires:CAAT for all individuals with abnormal spirometry or CRD.^34^ACQ-7 for individuals with isolated or overlapping asthma.^36^Basic information about access to health services for diagnosis and treatment will be provided to participants with abnormal spirometry and diagnosis of CRD.Qualitative interviews with individuals selected to reflect diversity of participants (n=30) to explore their healthcare experiences, particularly regarding access to respiratory diagnosis and care.

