SBQ: The SBQ questionnaire^32^ will be administered to compare performance with COLA-6 (MARES-1). The SBQ consists of 11 questions covering age, smoking history, body mass index, cough, wheezing, allergies, dyspnoea, exposure to dust or chemical particles and the presence of respiratory diseases during childhood. A total score of ≥17 indicates a higher risk for COPD.^32^

FeNO measurement: FeNO will be measured using a portable analyser (FeNObreathe, Geratherm Medical Latin America, Brazil), following American Thoracic Society guidelines^38^ to assess type 2 airway inflammation (MARES-1 and MARES-3). Subjects will be seated comfortably and instructed to inhale through the mouthpiece for 2–3 s to total lung capacity, followed by a steady exhalation lasting at least 6 s, without air leakage. An expiratory flow rate of 50 mL/s will be maintained, monitored by a sound signal. Up to six manoeuvres will be allowed, with 30 s intervals between attempts. The highest value among three acceptable measurements will be used, ensuring quality control by limiting deviation to ≤2.5 ppb or 10% within 15 min. FeNO levels will be classified as low/normal (<25 ppb), intermediate (25–50 ppb) or high (>50 ppb).^39^

Spirometry: Lung function will be assessed using a portable spirometer (Spirobank II Advanced, MIR, USA) to confirm or exclude CRDs (MARES-1 and MARES-3). Testing will follow American Thoracic Society and European Respiratory Society standards, ensuring A or B quality grades. ^40 41^At least three forced, acceptable and reproducible manoeuvres will be performed before and 20 min after inhalation of 400 mcg of salbutamol sulfate. Spirometry results will be reviewed and interpreted by a board-certified pulmonologist.

Participants will be classified based on spirometry and FeNO results (figure 2) into two groups, primarily according to the recommendations of the Global Initiative for Chronic Obstructive Lung Disease^42^ and the Global Initiative for Asthma.^27^

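### MARES-2 patients have their first study spirometry and FeNO 6 months after COLA-6, so the planned CRD proportion reflects status after possible treatment and can understate CRD at the time of COLA-6, mainly asthma

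*Protocol article*

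**What the plan says.** - **At COLA-6 (MARES-2, Phase 1).** Patients scoring as high risk receive a leaflet with "basic guidance about pulmonary health and how to access diagnostic and treatment services for respiratory conditions". The COLA-6 paragraph under Assessments adds that they are given their result and educational material.
- **At MARES-2 enrolment (Phase 2).** After consent the research team carries out an initial assessment. No spirometry or FeNO is listed. Under Assessments, both tests are assigned to MARES-1 and MARES-3 only.
- **First study test (MARES-3).** High-risk MARES-2 patients "will be contacted for a follow-up visit 6 months after their initial participation", and FeNO and spirometry are done at that visit.
- **Classification (Assessments and the Figure 2 caption).** Participants are classified from spirometry and FeNO.
- **Planned estimate (Data analysis, MARES-3).** "For patients from MARES-2, the proportions diagnosed with CRDs at spirometry will be calculated". The same paragraph treats only MARES-1 patients as having longitudinal data, and for them it reports the proportion whose spirometry improves over the 6 months.
- **Other data at the visit (Assessments, Interview with patients).** A questionnaire given to all participants collects "information on healthcare access, type of treatment received, medication access and treatment adherence". Nothing in the article links these answers to the CRD proportion.

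**The concern.** The study prompts high-risk patients to seek care, waits 6 months, and only then runs the test that decides whether they have a CRD. Someone whom the health services diagnosed with asthma and treated in the interval may have normal spirometry and low FeNO on the day. Under the stated rule that person counts as having no CRD. MARES-1 patients are protected by a baseline test; MARES-2 patients are not.

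What is at stake is how the figure is read. It is the planned spirometric follow-up of patients whom primary care professionals, rather than researchers, scored as high risk. Readers will naturally take it as the share of those patients who truly had a CRD. Without a label or a split by treatment, some patients who obtained effective care would be indistinguishable from patients who never had a CRD.

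**Working it through.** **1. Timing.** Set side by side, the sections give this order for a high-risk MARES-2 patient: COLA-6 and leaflet; consent and initial assessment without lung function tests; 6 months in which care may be sought; first study spirometry and FeNO; CRD proportion computed from that visit. The protocol itself allows for change over such an interval, since it plans to report improved spirometry and mean FeNO change in MARES-1 patients.

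**2. The plan's own counts (Sample size; Study design overview).**
- High risk in MARES-2: 1000 × 0.164 = 164, leaving 836 at low risk.
- Abnormal in MARES-1: 146 + 77 + 86 = 309.
- MARES-3 total: 309 + 164 = 473.

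All of these match the stated figures.

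**3. Implied CRD cases among the 164.** The article does not state these. They are the expected MARES-3 counts minus the MARES-1 counts:

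| Condition | MARES-3 − MARES-1 | Cases | Share of 164 |
|---|---|---|---|
| COPD | 218 − 146 | 72 | 43.9% |
| Asthma | 100 − 77 | 23 | 14.0% |
| PRISm | 100 − 86 | 14 | 8.5% |
| Total | 418 − 309 | 109 | 66.5% |

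Two cautions apply. The MARES-3 counts are given as upper figures (up to). The PRISm row subtracts a MARES-1 category that also includes restriction.

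**4. Sensitivity to treated asthma testing normal.** Let f be the fraction of the 23 asthma cases that are treated in the interval and test normal at 6 months. The document gives no value for f, so this is an assumption shown over a range.

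Asthma proportion = 23(1 − f)/164. Overall proportion = (72 + 23(1 − f) + 14)/164.

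| f | Asthma | Overall |
|---|---|---|
| 0 | 14.0% | 66.5% |
| 10% | 12.6% | 65.1% |
| 25% | 10.5% | 63.0% |
| 50% | 7.0% | 59.5% |
| 100% | 0% | 52.4% |

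If only asthma is affected, the overall figure can fall by at most 14.0 percentage points.

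**5. Comparison with sampling error.** The 95% CI for 109/164 is 0.665 ± 1.96 × √(0.665 × 0.335/164), which is 59.2% to 73.7%. The overall value at f = 50% lies just inside it. In relative terms the effect on the asthma figure is much larger, as that figure halves.

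**The case against.** The strongest reply is that the proportion carries little weight. It is not among the outcomes in Table 2. The MARES-2 and MARES-3 objectives are feasibility and access. COLA-6 accuracy belongs to MARES-1, where questionnaire and spirometry take place at the same visit and predictive values at the threshold of 4 are planned. The wording says truthfully that the diagnosis is made at spirometry, and the article never calls the figure a predictive value. All of this stands, and it makes the point a modest one.

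Other parts of the reply also stand in part:
- **Size.** The introduction describes spirometry as scarce in Brazil, so interval diagnosis may be uncommon and the bias small. The documents cannot settle this.
- **Figure 2.** It is not shown, and a rule there using prior diagnosis or treatment would soften the point. Its caption names only spirometry and FeNO.
- **Earlier treatment.** Table 1 does not exclude people already treated for a CRD, so a normal test in a treated patient is not peculiar to the 6-month delay. This argues for showing such patients separately.
- **Analysis detail.** Splitting a proportion by treatment is often left to an analysis plan. Here, however, the article does state a rule, and that rule can count a treated case as having no CRD.

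A reader might infer more than the document supports. One inference is that anyone diagnosed and treated would test normal. The mechanism is argued mainly for asthma, and nothing in the article supports applying the same loss to the 72 implied COPD cases. Another is that units with good access would appear to have more COLA-6 false positives. No comparison between units is planned.

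**Conclusion.** The point holds in a limited form. The MARES-2 proportion is measured after the study has directed patients to care, so it describes status at 6 months. As an estimate of CRD at the time of COLA-6 it can be too low, chiefly for asthma. CRD arising within the 6 months would push slightly the other way.

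The size is unknown. The ranges in the working rest on an assumed f of 10% to 50% and on case counts derived by subtracting expected numbers, so they illustrate the effect and do not estimate it. The document does not support reading this as a flaw in the study's main accuracy analysis, which uses same-visit spirometry in MARES-1. It is a cheap improvement to a secondary descriptive result.

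**What to change.** 1. Keep the spirometry-based proportion for MARES-2 patients, but label it as status at the 6-month visit, after possible care.
2. Report it split by whether respiratory treatment was started between COLA-6 and the visit, using the access and treatment questionnaire. Show patients already treated before COLA-6 as a separate group.
3. As a sensitivity analysis, report the proportion that also counts patients with a documented CRD diagnosis made by a health service in the interval. Do not call these cases confirmed CRD.

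**Cost.** A few analysis definitions, with no extra visit or test. The team should check before data collection that the questionnaire records an interval diagnosis and the timing of treatment explicitly, because the article's description does not name either. The downside is small: service diagnoses may lack spirometric confirmation, so the figure in step 3 should be presented as an upper estimate beside the spirometry-based one.
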